**Figure 1 f1:**
[figure not shown]
Diagram of participant flow through the trial.

The study has been reviewed by the Research Ethics Board of the Canadian College of Naturopathic Medicine and the Research Ethics Board of Sunnybrook Health Sciences Centre. Any amendments to this protocol will be communicated to the Research Ethics Board and Health Canada (the authority responsible for approval, conduct, oversight, and inspection of clinical trials in Canada) and modified on the trial registry.

### Participant eligibility

#### Inclusion criteria

A person aged 18–43 years old.At 12–35 weeks of gestation at the time of enrolment.Uniparous pregnancy.A nonsmoker, alcohol, or recreational drug user.Financially stable.In a married or common-law relationship.Clinical diagnosis of lifetime depression/anxiety or PDA (stable since the conception of the current pregnancy).No other significant comorbidities.Ability to read in English and provide informed consent.

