There is emerging evidence that the gut–brain axis (GBA) is a reasonable target for the management of PDA disorders. The GBA is a recently realized phenomenon in medicine, suggesting continuous bidirectional communication between the gut microbial community and the brain, a requirement for achieving and maintaining gastrointestinal homeostasis and cognitive function. Dysbiosis—an imbalance in bacterial composition—has been implicated in many disorders, including mental health (8). Thus, optimizing the health of the gut microbiome (i.e., treating dysbiosis) may be a logical approach to preventing and treating mood disorders.

Pregnancy itself has been associated with changes in the gut microbiome driven by immunological, hormonal, and metabolic changes—these changes are proinflammatory in nature, leading to an increase in cytokines and leukocytes and the recruitment of other immune cells (macrophages, natural killer cells, etc.) that aid in angiogenesis, transport of respiratory gases and nutrients between mother and fetus, and protection against pathogens (9). Interestingly, certain changes in the composition of the microbiome have been associated with various diseases during pregnancy, such as gestational diabetes, preeclampsia, fetal growth restriction, and obesity (9). Likewise, these changes are thought to be at least partially at play in perinatal mood disorders. A 2022 mini-review examined the correlation between perinatal depression and dysbiosis of the mother’s microbiome and reported dysbiosis as a likely precipitating factor in the development of psychiatric disorders during pregnancy (10). Emerging evidence suggests that nutritional interventions, with fish oils, probiotics, and prebiotics may play a favorable role in neuropsychiatric outcomes (11–16) and that some of these effects are mediated at least partially, by restoring eubiosis.

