## Methods

### Trial design and setting

This is a single-centered, partially randomized placebo-controlled double-blind feasibility trial with three intervention arms (Gutopia, Gutboost, and Gutless) and one active control. In total, 100 pregnant women with a history of depression and/or anxiety/PDA attending Sunnybrook Hospital Clinics in the Greater Toronto Area will be recruited.

Participants in Gutopia will receive a daily dose of both investigational products and dietary counseling on increasing dietary fiber. Participants in Gutboost will receive a daily dose of both investigational supplements, while participants in the Gutless arm will receive fish oil and a placebo. Participants in Gutless and Gutboost will be blinded to the status of the placebo/probiotic they will be receiving. The study member interacting with the patients will also be blinded to the treatment group the participant is assigned to. Participants who fully consent to receiving both investigational products, including placebo, will be fully randomized to one of the intervention arms. Participants not willing or able to take a placebo or probiotics will be assigned (not randomized) to the appropriate group that accommodates their preferences/needs. Participants unable or unwilling to take any of our investigational products will be assigned to the active control arm. Women in the control arm will receive standard care offered to all obstetric patients seen at the hospital.

The study involves six study visits, all of which can be conducted virtually every 3 months from the time of enrollment (**Figure 1**). The last study visit will happen between 9 and 12 months postpartum. Two of the study visits will occur during pregnancy [enrollment (visit 1) and third trimester (visit 2)], with the remaining occurring at 1, 3, 6, and 9 months postpartum. At all study visits, information on diet, mental health, physical activity, and sleep quality will be collected. Additionally, all participants will provide a stool sample at each visit, using our stool collection kits, which will be shipped to or dropped off at our center.

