##### Microbial response to diet and supplementation

First, we will assess the microbiome response to each intervention within each group by comparing changes in microbiome composition between baseline (preintervention) and follow-up visits (visits 2–6). The gut profile will be compared between all four arms at each follow-up. The within-group changes from baseline will be compared between groups.

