#### Statistical analysis

Should the trial succeed and we continue to recruit for a larger trial, the following statistical plan will be used to compare mental health outcomes between the groups: we will use mental health scores as the primary outcome and an intent-to-treat approach for these analyses.

Participants lost to follow-up will be assumed to have lost interest/commitment to the study and will be excluded from the analysis. Those who discontinue treatment will still be included.

Between-group differences for EPDS/GAD-7 scores will be analyzed using analysis of covariance (ANCOVA), with group membership as the independent variable, EPDS/GAD-7 as dependent, and pharmacotherapy, exercise status, and any form of psychotherapy as covariates.

The interaction effect between the O3FA and probiotics model will be analyzed and reported in each model. Alternative models will be used if the assumptions of ANCOVA are violated. If differences are found between groups, appropriate *post-hoc* analyses will be conducted to identify where the differences lie. Within-group differences at each time point will be analyzed using repeated measures ANOVA. Data from each follow-up will be compared to baseline scores. EPDS/GAD-7 scores will be the dependent variables, and follow-up times will be our independent variable.

Each stool sample will undergo shotgun metagenomics for taxonomic and functional output readings. A comprehensive analysis of all findings will be conducted by an experienced bioinformatics expert at Zymo Research. All researchers involved in the stool analysis will be blinded to the type of intervention. The relationship between each intervention and the relationship to EPDS and GAD-7 scores will be analyzed and reported by an experienced bioinformatician.

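### The EPDS/GAD-7 ANCOVA omits gestational age at enrolment, although women may enter anywhere from 12 to 35 weeks (minor)

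*Protocol article*

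**What the plan says.** The Inclusion criteria section of the protocol article sets the entry window: "At 12–35 weeks of gestation at the time of enrolment". It also requires a history of depression, anxiety or PDA that has been "stable since the conception of the current pregnancy".

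Trial design and setting places visit 1 at enrolment and visit 2 in the third trimester, "with the remaining occurring at 1, 3, 6, and 9 months postpartum". It adds: "The last study visit will happen between 9 and 12 months postpartum". The same section assigns women who cannot or will not take any study product to the control arm without randomisation. Women who decline only placebo or probiotics are also placed by preference.

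Randomisation is stratified by antidepressant or anxiolytic treatment only (text under Exclusion criteria).

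The Statistical analysis section gives the model for EPDS and GAD-7: ANCOVA with arm as the factor and "pharmacotherapy, exercise status, and any form of psychotherapy as covariates". It is introduced as the plan to be used if the feasibility trial succeeds and recruitment continues. For the microbiome, the article says "The gut profile will be compared between all four arms at each follow-up" and that changes from baseline will be compared between groups. No covariates are named there.

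**The concern.** A 23-week entry window means that women in the same arm reach the same visit after very different lengths of antenatal participation. Week of entry is a baseline quantity, fixed before allocation and already on record, and it could plausibly be related to the EPDS and GAD-7 scores. The article does not leave the covariates open. It fixes a list of three, and following that list as written excludes this one.

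Two things are at stake. Among randomised women, any outcome variation explained by entry week stays in the error term, and a chance difference between arms in mean entry week is carried into the estimated arm effect. In the comparison of the intervention arms (75 women) with the control arm (25 women), nothing in the design makes entry week alike. The Discussion nevertheless expects that comparison to inform the size and direction of changes.

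**Working it through.** The article gives no figure for this point, so there is none to reproduce. The check asks how much entry week can vary and how far arms can differ by chance.

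**Inputs**
- Entry window: 12 to 35 weeks (Inclusion criteria).
- Postpartum follow-up: visits at 1, 3, 6 and 9 months, the last between 9 and 12 months, taken as 39 to 52 weeks (Trial design and setting).
- Arm sizes: 75 intervention and 25 control (Discussion). An equal split of the 75 gives 25 per arm.
- Assumption: delivery at 40 weeks, with 37 to 41 as the range.
- Assumption, for illustration only: entry is uniform over the window.

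**Antenatal time on study** = delivery week − entry week
- Delivery at 40: 40 − 12 = 28 weeks against 40 − 35 = 5 weeks; ratio 28/5 = 5.6.
- Delivery at 37: 25/2 = 12.5. Delivery at 41: 29/6 = 4.8.

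**Time on study to 1 month postpartum** (adding 4.3 weeks)
- 32.3 against 9.3 weeks; ratio 3.5.

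**Time on study to the end of follow-up**
- To 9 months: (28 + 39)/(5 + 39) = 67/44 = 1.5.
- To 12 months: (28 + 52)/(5 + 52) = 80/57 = 1.4.

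The spread is therefore large before delivery and at the first postpartum visit, and modest by the end.

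**Chance imbalance between two randomised arms of 25**
- SD of uniform entry = (35 − 12)/√12 = 6.64 weeks.
- SE of the difference in means = 6.64 × √(2/25) = 1.88 weeks.
- 95% range = ±1.96 × 1.88 = ±3.7 weeks.
- In 200,000 simulated trials under the same assumptions, some pair of the three intervention arms differed by more than 3 weeks in about 25%.

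**Effect on the estimate.** If the score changes by β points per week of entry, an imbalance of d weeks moves the unadjusted arm difference by β × d. If ρ is the correlation of entry week with the score given the other covariates, adjustment multiplies the residual variance by 1 − ρ². The article gives neither β nor ρ, so the size in scale points cannot be stated.

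**The case against.** **These are not the trial's main analyses.** The primary outcome is process evaluation, mental-health and microbiome data are exploratory, and the ANCOVA is meant for a larger trial. This stands and sets the priority. The 1.9-week standard error also belongs to the feasibility size and shrinks as arms grow.

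**Randomisation balances entry week in expectation.** This stands as far as bias is concerned. It does not recover the lost precision, and it does not cover women placed by preference.

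**Nothing shows that decliners enter at other gestations.** They come through the same clinics and the same screening call. This stands: confounding is possible, not demonstrated. Self-selection by willingness to take supplements is the larger problem with that arm, and a gestation covariate does not repair it.

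A reader might also infer four stronger things that the article does not support.

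- *Late entrants are selected survivors with much lower relapse risk.* The Background cites relapse of 40% without a time window. Spreading it evenly over 40 weeks is an assumption: h = −ln(0.6)/40 = 0.0128 per week, and 1 − exp(−28h) = 30% against 1 − exp(−5h) = 6%. A constant hazard has no memory, so this contrast reflects only the weeks remaining and says nothing about past stability. Antenatal relapse is also not the outcome. Scores at visits are, and four of the five follow-up visits are postpartum.
- *Total exposure differs several-fold.* It does so before delivery, but not over the whole follow-up.
- *The article itself says that the pregnancy stage of the baseline stool matters.* It says "Pregnancy itself has been associated with changes in the gut microbiome", which does not distinguish weeks or trimesters.
- *The microbiome comparisons are wrong because they name no covariates.* They are a brief outline, and such detail is commonly left to a fuller plan.

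**Conclusion.** The point holds as a minor improvement to a stated model. The covariate list for EPDS/GAD-7 omits a baseline variable that is known for every woman and ranges over 23 weeks. Antenatal time on study varies 5.6-fold if delivery is at 40 weeks (4.8-fold at 41, 12.5-fold at 37), but only about 1.5-fold to 9 months postpartum.

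For randomised women the consequence is lost precision and unadjusted chance imbalance, with a standard error of about 1.9 weeks between two arms of 25. That figure rests on uniform entry and an equal split. It is not bias. For comparisons with the preference-assigned control arm, a possible confounder is left unadjusted, and adjusting for it would still leave self-selection.

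The size of the effect on the scores cannot be derived from the article.

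**What to change.** In the Statistical analysis section, add gestational age at enrolment, as a continuous baseline covariate, to the EPDS/GAD-7 ANCOVA. Use the same covariate when between-arm changes in the microbiome from baseline are modelled.

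If dependence on exposure is explored at visits 2 and 3, use gestational age at enrolment or its interaction with arm. Do not use weeks of supplement actually taken: that quantity arises after randomisation, reflects adherence, depends on the delivery date at visit 3, and is undefined for controls.

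Reports of the comparison with the control arm should say that adjustment for entry week does not make the groups comparable.

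The cost is a change of wording and one degree of freedom for the covariate, with a little more if the interaction is explored. No new data are needed, because eligibility screening already records the value.

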## Background

Perinatal depression and anxiety (PDA) is prevalent in new and expectant mothers, affecting millions of women worldwide. Recent evidence suggests that one in seven women in the 20th–28th week of gestation develop depression, which impacts their ability to return to normal functioning; in the same period of gestation, anxiety has a prevalence of about 8.5%–10.5% (1). A recent meta-analysis included nine studies, with a total of 4,449 participants, examining prevalence rates of generalized anxiety disorder throughout pregnancy. Studies took place in Germany, Brazil, Italy, the UK, Turkey, Nigeria, France, and Sweden. Prevalence rates were found to range from 0.9% to 22.7%, with pooled data analysis revealing an overall prevalence of 3% (2). The pooled prevalence of antenatal depression reported in a 2021 meta-analysis of 173 studies published before 2019 was 20.7% (3). Well-known risk factors for perinatal depression include poor social support, chronic and persistent health issues in their infant, an abusive partner, marital difficulties, familial history, a history of violence, and other negative life events (4). The strongest predictor of perinatal depression, however, is a history of mood or anxiety disorders (4). Those with a history of depression have a 20-fold higher risk of a subsequent pregnancy (5), and relapse rates of 40% have been observed (4). Risk factors for new-onset perinatal anxiety can include low education, living with extended family members, a family history of psychiatric disorders, a history of sleep disorders, multiparity, and other negative life events. However, the most significant risk factor for worsening perinatal anxiety was having a comorbid psychiatric disorder, such as depression (6). Available treatment options for these disorders in the peripartum population include pharmacotherapy and psychotherapy. However, safety concerns for pharmacological treatments during pregnancy and lactation, limited access to care for psychotherapy, and the stigma of mental illness are major barriers to implementing these treatment options (7). Moreover, lack of treatment is associated with morbidity for the mother, infant, and family system and impairment in quality of life (7). Acceptable and readily available treatment alternatives are urgently required.

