#### Exclusion criteria

Prepregnancy BMI > 30.Low income (unable to afford basic daily needs).Single parents without any kind of family support.Having a child with significant mental/physical disability.Previously diagnosed with other major mental health disorders.Taking prescription medications (other than SSRIs/SNRIs/TCA).Smoking and recreational drug use.Dietary restrictions or allergies to fish oils.Repeated antibiotic use.Women are unable to switch to study brand supplements.Multiparous women with young children (i.e., one or more children less than 4 years of age at the time of delivery).No/low English reading comprehension.

Our inclusion criteria allow for antidepressant/anxiety use. Medication use is an important prognostic factor that can significantly alter mental health outcomes. Hence, the number of patients treated with an antidepressant/anxiolytic needs to be equally distributed among all arms. To achieve this, we will use stratified randomization using two strata (treated vs. untreated) through a computer-generated process using permuted blocks of three and six. The process will be repeated separately for untreated participants.

Preexisting and diagnosed major mental health disorders will be determined at the time of screening using a modified version of the Mini International Neuropsychiatric Interview (MINI). The MINI, conducted by a trained research team member, will allow for confirmation of a history of anxiety/depression and an absence of current anxiety/depression and other major mental health disorders (bipolar, schizophrenia, psychosis, etc.).

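### The EPDS/GAD-7 model leaves out type of psychiatric history, which matters mainly for comparisons with the non-randomised control arm and preference-assigned women

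*Protocol article*

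**What the plan says.** - **Who enters.** Trial design and setting describes the population as "In total, 100 pregnant women with a history of depression and/or anxiety/PDA". The inclusion criterion reads "Clinical diagnosis of lifetime depression/anxiety or PDA (stable since the conception of the current pregnancy". Depression only, anxiety only and both are therefore all eligible.
- **What is known about risk.** The Background says that "the most significant risk factor for worsening perinatal anxiety was having a comorbid psychiatric disorder, such as depression". For perinatal depression it says: "The strongest predictor of perinatal depression, however, is a history of mood or anxiety disorders".
- **What is measured before allocation.** Under Exclusion criteria, a modified MINI at screening "will allow for confirmation of a history of anxiety/depression and an absence of current anxiety/depression".
- **What is balanced.** The same section stratifies randomisation on one factor, treated versus untreated with an antidepressant or anxiolytic, because medication is prognostic.
- **What is modelled.** Statistical analysis sets out an ANCOVA with group as the independent variable, "EPDS/GAD-7 as dependent, and pharmacotherapy, exercise status, and any form of psychotherapy as covariates". Type of history is not listed.
- **How women reach the arms.** Trial design and setting randomises only women who accept both products and the placebo. Others are assigned to an arm that suits them, and those who cannot or will not take any product form the control arm.
- **Which comparisons are planned.** Mental health outcome plans between-group comparisons of EPDS and GAD-7. The Discussion expects the 75 intervention women against the 25 controls to inform the size and direction of change.

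**The concern.** The protocol itself reports that psychiatric comorbidity bears on worsening anxiety, GAD-7 is one of its two mental health outcomes, and its entry criteria admit women with and without that comorbidity in their history. It balances medication because medication is prognostic, but type of history enters neither the strata nor the model. History is fixed before allocation, so treatment cannot affect it, and the MINI already touches on it.

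What is at stake depends on the comparison. Between randomised arms, the mix of histories can differ only by chance. Between the intervention arms and the control arm, or wherever preference-assigned women contribute, the mix may differ for reasons tied to why a woman accepted or declined the products. Recruitment from both obstetric clinics and a mood and anxiety clinic makes a varied mix plausible. Stratification cannot protect those contrasts; adjustment for measured factors can, in part. A difference in who was at risk could otherwise be read as an arm effect.

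**Working it through.** **The plan's own figures.** 75 + 25 = 100, and 75 / 3 = 25 per intervention arm if the arms are equal. No alpha, power, effect size or SD is given, so the sample size cannot be reproduced by formula and nothing in it is contradicted.

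**Assumptions.** The documents do not give the mix of histories or their effect on scores. I assume a share p = 0.5 with the higher-risk history, a mean EPDS gap of 2 points (range 1 to 3) and SD 5.

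**1. Randomised arms, chance imbalance.** With X and Y independent Bin(25, p), P(|X − Y| ≥ 5), which is a difference of 20 percentage points or more:

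| p | two given arms | any pair of the three arms (simulated) |
|---|---|---|
| 0.2 | 0.110 | 0.244 |
| 0.3 | 0.164 | 0.343 |
| 0.4 | 0.193 | 0.394 |
| 0.5 | 0.203 | 0.409 |

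**2. Effect of such an imbalance.** Shift = imbalance × gap = 0.20 × 2 = 0.4 points (0.20 × 1 = 0.2; 0.20 × 3 = 0.6). Standard error of a two-arm difference = 5 × √(2/25) = 1.41. The shift is 0.4 / 1.41 = 0.28 standard errors. On a standardised scale, with an assumed gap of 0.3 to 0.8 SD, the shift is 0.06 to 0.16 SD. The smallest difference detectable with 80% power (two-sided 5%) is (1.96 + 0.84) × √(2/25) = 0.79 SD.

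**3. Precision gained by adjusting.** R² = p(1 − p) × gap² / SD² = 0.25 × 4 / 25 = 0.04 (0.01 for a gap of 1, 0.09 for 3). The standard error is multiplied by √(1 − R²): √0.96 = 0.98, a cut of about 2% (√0.99 and √0.91 give about 0.5% and 5%), before the degrees of freedom are spent.

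**4. A larger trial.** With an assumed 100 per arm and p = 0.5, the SD of the difference in proportions is √(2 × 0.25 / 100) = 0.071. A 20-point gap is then 0.20 / 0.071 = 2.8 SDs, with a chance below 1%.

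**5. Control and preference-assigned women.** The same formula, imbalance × gap, applies, but the imbalance is not limited by chance and does not shrink as the trial grows. At 20 percentage points the shift is again 0.4 points (0.2 to 0.6), and it rises in proportion to the imbalance. The documents give no way to say how large the imbalance will be, or in which direction.

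**The case against.** The other side has several sound points.

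- **The Background supports less than a reader might infer.** It is tempting to say that the protocol names comorbid depression as the leading risk factor and ranks the histories by risk. It does not. Depression is given as an example of a comorbid disorder, and the statement is about worsening anxiety only. For perinatal depression the text names a history of mood or anxiety disorders together, which every participant has. The 40% relapse rate has no anxiety-only comparator. Nothing ranks the three histories for EPDS.
- **Women are well at entry.** The MINI must show "confirmation of a history of anxiety/depression and an absence of current anxiety/depression and other major mental health disorders". Carrying a statement about comorbid disorder over to type of lifetime history is an inference.
- **The model is conditional.** The ANCOVA is for a larger trial if this one succeeds. Process evaluation is the primary outcome and is untouched.
- **No rule is broken.** Stratifying on medication is no commitment to balance every prognostic factor. Among randomised arms, chance imbalance is not bias, and the standard error already allows for it.
- **Baseline scores may carry some of the information.** No EPDS or GAD-7 ceiling is set at entry, both are measured at baseline, and changes from baseline are planned.
- **The control arm has a larger problem.** It is formed by preference, history is one of many possible confounders, and nothing shows that history is related to willingness to take supplements.

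All of this stands, and it limits the weight of the point. It does not remove it. Microbiome profiling says that enrolment would continue into the larger trial, so the outlined model would serve an extension of this trial. The between-group score comparisons under Mental health outcome carry no such condition. The covariates are a stated choice, not detail left for later.

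**Conclusion.** The point holds in a limited form, as an optional improvement. Type of lifetime history is absent from the stated EPDS/GAD-7 model although the protocol gives some reason to think it prognostic, at least for anxiety.

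A reader might infer that the omission biases the trial or that the strata must change. The documents support neither. Between randomised arms there is no bias, and the loss is about 2% of the standard error (0.5% to 5%) on assumed inputs. The 11% to 20% chance of a 20-point imbalance applies at 25 randomised women per arm and largely disappears in a larger trial.

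What remains is the comparison with the control arm and with preference-assigned women, where the mix of histories may differ systematically. The shift there is imbalance × gap, about 0.4 EPDS points per 20 percentage points under the assumed 2-point gap, with no limit set by chance. That such an imbalance will occur is a possibility, not something the documents show.

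**What to change.** In Statistical analysis, add lifetime diagnostic history from the screening MINI, in three levels (depression only, anxiety only, both), as a pre-specified baseline covariate in the EPDS and GAD-7 models. It should stand alongside the baseline score, not replace it. Tabulate it by arm, split by randomised and assigned women. The strata need no change.

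One practical condition applies: the article says that the modified MINI confirms a history, but not that the three categories are stored separately. The screening form should record them as such.

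The cost is a sentence of analysis text and two degrees of freedom (one if history is reduced to two levels). No extra visits or participants are needed. The adjustment removes one measured source of confounding in the control-arm comparison and leaves the rest, so that comparison should still be reported as non-randomised.
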